## 9.2 Recruitment visit and screening assessment (Visit 1)

Once the subjects have agreed to participate in the study, they will be invited for the recruitment visit, when the following activities will be performed by the research team:

- written informed consent/assent
- checking inclusion and exclusion criteria
- medical (diabetes) history
- body weight and height measurement; calculation of BMI
- blood pressure measurement

- record of current insulin therapy
- urine pregnancy test (females of child-bearing potential)

### 9.2.1 Screening and reference blood sampling

If not done at diagnosis, a blood sample will be taken for assessment of full blood count, thyroid function (TSH, fT4), anti-transglutaminase antibodies and IgA (all measured at a local laboratory). Less than 15 ml of whole blood will be taken from each participant if need be.

## 9.3 Baseline visit (Visit 2)

Subject will arrive at the clinical facility in the morning at the agreed time. This session will include the following activities:

- Body weight measurement (see 12.1.1)
- Cognitive function will be assessed using validated computerized cognitive tests (see 12.2.2)
- A mixed meal tolerance test (MMTT) to assess residual beta cell function (see 12.1.2).
- In addition to measurements of C-peptide and blood glucose (MMTT), blood samples for analysis of HbA1c, lipid profile and immunological parameters will be taken (see 12.4)
- Validated questionnaires will be distributed to assess quality of life and diabetes management (see 12.2.1).
- At the end of this session, participants will be fitted with a blinded continuous glucose monitoring (CGM) device to assess baseline glycaemic control. Instructions on how to safely remove and send back the device will be provided (see 12.1.3.1)

## 9.4 Run in period

All participants will receive core diabetes training as per usual clinical practice during an up to three week run-in period following diagnosis, study consent/assent and baseline assessment. These non-study-specific training sessions should include introduction to blood glucose monitoring, blood glucose targets, insulin therapy (including handling of insulin pens and injections), physical activity advice, hypoglycaemia management, dealing with hyperglycaemia (incl. blood ketone monitoring), sick day rules, and carbohydrate counting (for details see section 8.2).

All subjects will be provided with 24 hour telephone helpline and will also be given written instructions about when to contact clinical team.

## 9.5 Randomisation

On completion of Visit 2, eligible subjects will be randomised in a 1:1 ratio using central randomisation software to the use of day and night closed loop or to standard therapy. The randomisation will be stratified by site, age, and possibly gender.

## 9.6 Post-randomisation training (Visits 3 and 4)

### 9.6.1 Closed loop intervention

Participants randomised to the closed loop group will receive additional training sessions following randomisation to cover key aspects of insulin pump use and CGM, prior to starting closed loop insulin delivery. Particular attention will be paid to:

- Insulin cartridge and infusion set changes and correct priming procedure
- Carbohydrate counting and the use of the bolus calculator on the pump
- Hypo- and hyperglycaemia management using an insulin pump
- Sensor insertion and calibration
- Uploading pump data

Written easy to use guidelines for the operation of insulin pump and CGM will be provided. This session will be conducted by a professional pump educator and/or member of the study team. Device manual guides will be provided. Competency on the use of study pump and CGM will be assessed.

Guidelines for health care professional with respect to initiation of insulin pump therapy and continuous glucose monitoring will be provided separately in the study manual.

### 9.6.2 Standard therapy (control intervention)

Following randomisation participants in the control group will receive additional training sessions to complement the core training as provided during the run-in: Particular attention will be paid to:

- Carbohydrate counting
- Understanding insulin to carb ratios and correction factors
- Data review, pattern recognition
- Adjusting insulin doses

Written easy to use guidelines will be provided. These sessions will be conducted by an experienced educator. Guidelines for health care professional with respect to multiple daily injection therapy will be provided separately in the study manual.

## 9.7 Initiation of treatment arm (Visit 5)

For participants competent in the accomplishment of their respective treatment regimen (MDI or pump and CGM), the start of study arm will be initiated within at least two weeks of visit 3, but within 6 weeks of diagnosis at latest. Initiation visits could be either done at the hospital clinic, the clinical facility, subject's home or other suitable meeting place. Current insulin therapy will be recorded.

Subjects will be provided with 24 hour telephone helpline and will also be given written instructions on how to deal with low and high glucose at home and when to contact study team.

### 9.7.1 Closed loop intervention

Those subjects randomised to closed loop intervention will receive training required for safe and effective use of the closed loop system and pump suspend feature. The visit will include training on connection and disconnection of the closed loop system, switching between closed loop and usual pump therapy and trouble-shooting aspects. Written step by step guidance will also be provided. During the initiation visit, subjects will use closed loop system under supervision by study staff. Subjects will have a meal according to their own choice and will be required to deliver a meal bolus for the given meal. Competency on the use of closed loop system will be assessed by the study team. Only subjects who demonstrate competency on use of the system will be allowed to continue to the home study phase. Participants are expected to use the closed loop at all times during the 24 months intervention period.

### 9.7.2 Standard therapy (control intervention)

In subjects randomised to control intervention, diabetes management skills will be revisited, data will be reviewed, and dose adjustments will be made if need be. Additionally, study schedule and study related procedures will be discussed again. In the control intervention arm, visit 5 can be done via telephone/email, too. Participants will apply standard insulin therapy using multiple daily injections via insulin pens during the 24 months control period. However, participants will be allowed to switch to insulin pump therapy if clinically indicated applying NICE criteria according to usual clinical practice. As per the intention to treat approach of this study, participants switching to insulin pump treatment during control intervention will continue to be followed up unless consent is withdrawn or other withdrawal criteria apply (see section 9.14).

## 9.8 Telephone/email contact after initiation of treatment arm

Participants and/or parents will be contacted by email or telephone within one week after initiation of the respective study arm. The purpose of this contact would be to troubleshoot any problems, and to record any adverse events, device deficiencies, and changes in insulin settings, other medical conditions and/or medication. Thereafter, participants will be followed up through study visits at 3-monthly intervals. Throughout the trial, subjects/parents and/or the clinical team are free to adjust insulin therapy as per usual clinical practice, but no active treatment optimisation will be undertaken by the study team.

## 9.9 Routine follow up visits (Visit 6, 8, 10, 11, 12)

The subjects will be invited to attend the first follow up visit 3 months after diagnosis. Thereafter, visits will take place every 3 months for the remainder of the study. Routine follow up visits can take place at the hospital clinic, home or other suitable meeting place, according to participants' convenience. A routine follow up visit should not take longer than approximately 30 minutes.

The purpose of this visit would be to record any adverse events, device deficiencies, and changes in insulin settings, other medical conditions and/or medication. An HbA1c sample will be taken to monitor overall glucose control. For subjects randomised to closed loop intervention, data from study devices will be downloaded.

At the end of this session, participants of both study arms will be fitted with a blinded continuous glucose monitoring (CGM) sensor. The sensor will be worn at home for up to 14 days. If the sensor fails (i.e. does not provide any data) or sensor function is interrupted prematurely (detached sensor), another sensor may be inserted. The sensor(s) will be sent back to the research team or collected by the research team once the sensor life has expired and/or the sensor has detached. The sensor data may be used to optimise insulin delivery. Sensors can be applied 2 weeks prior to the study visit and data reviewed at the study visit if required.

## 9.10 Follow up visits including MMTT (Visit 7, 9)

The subject will attend the research centre for the purpose of a mixed meal tolerance test (see section 12.1.2) at 6 months and 12 months after diagnosis. Otherwise, procedures are identical to routine follow up visit (including HbA1c sampling and blinded CGM; see section 9.9). Follow up visits including MMTT should not last longer than 3-4 hours.

- Body weight, height and blood pressure will be measured
- In addition to measurements of C-peptide and blood glucose (MMTT), blood samples for analysis of immunological parameters will be taken (see section 12.4). At 12 months, blood lipid profile will be additionally assessed

At the end of the session, participants will be fitted with the Actiwatch (a simple wristwatch used to measure sleep non-invasively in the participant's home), and the Pittsburgh Sleep Quality Index and a sleep diary will be handed out (see section 12.2.3). The wristwatch will be worn for up to 7 days. Concomitantly, a sleep diary will be kept, and PSQI questionnaires will be completed by the participants (assisted by their parents/carers if need be), and their parents/carers. The wristwatch, the completed diary and questionnaires, along with the blinded CGM device will be sent back to the research team or collected by the research team.

At 12 months, a subset of participants/family members in the closed loop arm will be invited to take part in a qualitative interview with the trained personnel (see 12.2.4.1).

At 12 months, cognitive function will be assessed using validated computerized cognitive tests (see section 12.2.2).

## 9.11 Penultimate visit 13

For assessment of glycaemic control during the final 3-month period of the trial, participants of both study arms will be asked to attend the clinical facility at least 2 weeks before the end of study visits (Visit 14). Alternatively, this visit could take place in the subject's home. Participants will be fitted with a blinded continuous glucose monitoring (CGM) sensor. The sensor will be worn at home for up to 14 days.

Additionally, participants will be fitted with the Actiwatch wristwatch, and the Pittsburgh Sleep Quality Index (PSQI) and a sleep diary will be handed out (details re sleep assessment see section 12.2.3) for assessment of sleep. The wristwatch will be worn for 7 days. Concomitantly, a sleep diary will be kept, and the PSQI will be completed by the participants (assisted by their parents/carers if need be), and their parents/carers.

All devices (blinded CGM, wristwatch) and the completed sleep diary and questionnaires, along with the blinded CGM device will be returned to the research team once the sensor life has expired and/or the sensor has detached, or at the end of study visit (Visit 14) at latest.

For those participants continuing with the extension phase, this visit can be combined with Visit 14.

## 9.12 End of study visit (Visit 14)

The subject will be invited to attend the research centre approximately 3 months after visit 12. This would be the end of 24 month study period. The subject will have a MMTT and a blood sample for HbA1c, immunological analyses and lipid profile will be taken. Body weight, height and blood pressure measurements will be made. Subject will be asked to complete questionnaires as outlined in section 12.2.1. Cognitive function will be assessed using validated computerized cognitive tests (see section 12.2.2). Additionally, subjects/family members will be invited to attend focus group discussions at their clinical site (see section 12.2.4.2) following the End of study visit. For participants of the closed loop intervention, who are not continuing with the extension phase, study device data will be downloaded and subjects will start transition to usual care.

## 9.13 Transition to usual care

Following visit 14, for those not wishing to continue in the extension phase, (or following Visit 17 for those completing the extension phase) subjects randomised to closed loop will revert to conventional insulin therapy by switching back to either insulin pump alone or multiple daily injection therapy as per decision of the clinical team. Refresher training sessions on standard therapy will be provided by the routine clinical team to facilitate transition to usual care over a period of up to 8 weeks. During this period, subjects will be able to continue using the study insulin pump and/or study CGM (but not closed-loop) as required to facilitate transition. Subjects of the control intervention will continue with standard therapy as before.

## 9.14 Optional extension phase

At 24 months, all subjects will be invited to continue in an extension phase of the study for a further 24 months with the treatment allocated at randomisation. Participants opting to continue with the extension phase will be asked to re-consent.

### 9.14.1 Routine follow up contacts

Participants and/or parents will be contacted every 3 months during the extension phase. This can be at routine clinic appointments or by email/telephone. The purpose of this contact would be to troubleshoot any problems, and to record any adverse events, device deficiencies, and changes in insulin requirements other medical conditions and/or medication. Local HbA1c values will be recorded at this visit. Throughout the extension phase, subjects/parents and/or the clinical team are

free to adjust insulin therapy as per usual clinical practice, but no active treatment optimisation will be undertaken by the study team.

### 9.14.2 Study visits

At 36 and 48 months after diagnosis, participants of both study arms will be invited to attend the research centre. The subject will have a fasting blood sample for C-peptide, glucose, HbA1c and lipids. Body weight and height measurements will be made. Subjects will be asked to complete questionnaires as outlined in section 12.2.1. Participants of both study arms will be fitted with a blinded continuous glucose monitoring (CGM) sensor. For the final study visit (Visit 17) the blinded CGM will be applied 2 weeks prior (Visit 16).

Participants in the control intervention arm already using a FreeStyle Libre continuous glucose monitoring sensor will be able to use their own sensor, rather than the study blinded sensor. The sensor will be worn at home for up to 14 days. If the sensor fails (i.e. does not provide any data) or sensor function is interrupted prematurely (detached sensor), another sensor may be inserted. The sensor(s) will be sent back to the research team or collected by the research team once the sensor life has expired and/or the sensor has detached. The sensor data may be used to optimise insulin delivery. Sensors can be applied 2 weeks prior to the study visit and data reviewed at the study visit if required.

At the end of the extension phase (Visit 17) at 48 months after diagnosis, subjects in the closed-loop arm will transition to usual care as described in 9.13.

## 9.15 Participant withdrawal criteria

The following pre-randomisation withdrawal criterion will apply:

1. Subject/Family is unable to demonstrate safe application of multiple daily injection therapy during run-in period as judged by the investigator

The following pre- and post-randomisation withdrawal criteria will apply:

2. Subject is unable to demonstrate safe use of MDI or study insulin pump and/or CGM during post randomisation training period as judged by the investigator
3. Subject fails to demonstrate compliance as described in sections 9.6.1 and 9.6.2 with MDI therapy or study insulin pump and / or CGM during post randomisation training period
4. Subjects may terminate participation in the study at any time without necessarily giving a reason and without any personal disadvantage

5. Significant protocol violation or non-compliance
6. Recurrent severe hypoglycaemia events not related to the use of the closed loop system
7. Recurrent severe hyperglycaemia event/DKA unrelated to infusion site failure and related to the use of the closed loop system
8. Decision by the investigator or the Sponsor that termination is in the subject's best medical interest
9. Allergic reaction to insulin
10. Allergic reaction to adhesive surface of infusion set or glucose sensor
11. If patient cannot be contacted in 12 weeks subject will be considered lost to follow up

If participant wishes to withdraw from trial treatment, sites should nevertheless explain the importance of remaining on trial follow-up or, failing this, of allowing routine follow-up data to be used for trial purpose. Generally, follow-up will continue unless the participant explicitly also withdraws consent for follow-up.

Subjects who are withdrawn for reasons stated in (5) to (11) will be invited to undergo mixed meal tolerance test and to provide blood sample at the end of the planned study intervention for the assessment of HbA1c.

In consenting to the trial, participants are consenting to trial treatment, follow-up and data collection. If voluntary withdrawal occurs, the participant (or parent/legal representative) should be asked to allow continuation of scheduled evaluations, complete an end-of-study evaluation, and be given appropriate care under medical supervision until symptoms of any adverse event resolved or the participant's condition becomes stable. Follow-up of these participants will be continued through the research nurse and the lead investigator at each site and, where these are unsuccessful, through child's local paediatric diabetes service or via their GP.

The research team plans to enable ongoing observation of participants as they move from paediatric to adult health care services. This ongoing observation will be the focus of a separate application for funding.

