| Criteria for withdrawal of patients on safety grounds | 
A subject, parent, or guardian may terminate participation in the study at any time without necessarily giving a reason and without any personal disadvantage. An investigator can stop the participation of a subject after consideration of the benefit/risk ratio. Possible reasons are:
 

1. Serious adverse events

2. Significant protocol violation or non-compliance

3. Failure to satisfy competency assessment

4. Decision by the investigator, or the Sponsor, that termination is in the subject's best medical interest

5. Pregnancy, planned pregnancy, or breast feeding

6. Allergic reaction to insulin

 
Efforts will be made to retain subjects in follow up for the final primary outcome assessment even if the intervention is discontinued, unless the investigator believes that it will be harmful for the subject to continue in the trial.
 |

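### Withdrawal criterion 6 in protocol 9.15 names severe hypoglycaemia but leaves out episodes related to the closed loop; a small wording correction is due

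*Combined protocol and SAP*

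**What the plan says.** Protocol 9.15 gives one pre-randomisation criterion and ten that apply before and after randomisation, numbered 1 to 11. Three matter here:

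- Criterion 6: "Recurrent severe hypoglycaemia events not related to the use of the closed loop system".
- Criterion 7: "Recurrent severe hyperglycaemia event/DKA unrelated to infusion site failure and related to the use of the closed loop system".
- Criterion 8, which begins "Decision by the investigator or the Sponsor that termination is in the" and ends with the subject's best medical interest.

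The synopsis has its own row, "Criteria for withdrawal of patients on safety grounds". It is permissive: "An investigator can stop the participation of a subject after consideration of the benefit/risk ratio". The first of its possible reasons is "1. Serious adverse events", with no condition on cause. Section 9.15 has no such item.

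On what happens after withdrawal, 9.15 says: "Subjects who are withdrawn for reasons stated in (5) to (11) will be invited to undergo mixed meal tolerance test", together with an HbA1c sample. It adds: "Generally, follow-up will continue unless the participant explicitly also withdraws consent for follow-up".

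**The concern.** Criterion 6 covers severe hypoglycaemia that the device did not cause and passes over severe hypoglycaemia that it did cause. A device trial most needs a stated rule for the second kind. Section 11.3.9 says that closed loop is expected to lower, but not remove, the risk of plasma glucose under 2.0 mmol/l. The users are aged 10 to 16.9 years, and the synopsis expects them to run the system for 24 months with nobody supervising or monitoring remotely. Under 11.2.3, a severe episode is one in which another person has to treat the participant because consciousness is altered.

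A site following 9.15 item by item finds a named rule for recurrent hypoglycaemia in the injection arm and none for recurrent hypoglycaemia attributed to the closed loop. Section 9.17 allows the study to be stopped after three consecutive safety withdrawals. The named withdrawal rule that would feed that trigger does not mention the device's main acute hazard.

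**Working it through.** The plan gives no figure on this point and no arithmetic is needed beyond counting. The check sets the texts side by side.

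**Step 1: read all 11 items in 9.15.** Items 1 to 3 concern competence and compliance in run-in and training. Item 4 is voluntary exit and item 5 is protocol violation or non-compliance. Item 6 is hypoglycaemia, item 7 hyperglycaemia or DKA, and item 8 judgement. Items 9 and 10 are allergies and item 11 is loss of contact. Items naming hypoglycaemia: 1 of 11. Items naming hypoglycaemia related to closed loop: 0 of 11.

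**Step 2: place recurrent events by type and by relation to closed loop.**

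| Recurrent event | Not related to closed loop | Related to closed loop |
|---|---|---|
| Severe hypoglycaemia | Criterion 6 | No specific criterion |
| Severe hyperglycaemia or DKA | No specific criterion | Criterion 7, unless due to infusion site failure |

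The two limits run in opposite directions, and the documents give no reason for it.

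**Step 3: look for other ways to act on the empty hypoglycaemia cell.**

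- Criterion 8 applies to any cause, in either arm, whether or not the event is serious. It rests on judgement.
- Criterion 4 lets the participant leave at any time. It is not a safety rule.
- The synopsis reason applies to any cause, but only to events classed as serious and only at the investigator's discretion. It does not appear in 9.15.

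DMEC advice does not belong on this list. In 9.17, 14.4 and 17.2 it concerns the study, not one participant's withdrawal.

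**Step 4: ask how often the synopsis reason would fail to reach such an episode.** Section 11.2.3 says that severe hypoglycaemia is not always a serious adverse event. Section 11.1.4 points the other way. It lists severe hypoglycaemia among the anticipated serious adverse events. It also asks that important events which put the subject in jeopardy, or need intervention to avert one of the listed outcomes, be treated as serious. Repeated episodes that meet the 11.2.3 definition of severe would usually satisfy that. The remaining cases, recurrent and device-related but judged non-serious, should be few, and criterion 8 still covers them.

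**Step 5: check the link to 9.17.** A withdrawal under criterion 8 made for safety counts as a safety withdrawal, so the trigger still works. But it depends on a judgement being made and recorded as safety-related, where a named criterion would supply the reason directly.

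**The case against.** The strongest reply is that nobody is left unprotected. Criterion 8 already permits withdrawal for device-caused hypoglycaemia. It falls inside the range of items whose holders are invited to the mixed meal test and HbA1c sample. The synopsis belongs to the same protocol and is not cancelled because 9.15 does not repeat it. Section 11.1.4 makes most such episodes serious. All of this stands, and it is why the point is minor.

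A second reply is that the correction does not remove judgement. Recurrence is not defined, and the added item would be discretionary. A broader criterion 6 might also push sites to withdraw a participant when stopping or correcting the device would do. The first part stands: the change does not remove judgement, it only stops the text from excluding the device. The second part is met by the follow-up provisions. Section 9.15 continues follow-up unless consent to it is also withdrawn, and the synopsis asks for efforts to keep participants for the primary assessment after the intervention stops.

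Three stronger readings are tempting, and the documents do not support them:

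- A reader might infer that a participant with recurrent device-caused hypoglycaemia cannot be withdrawn. Criteria 4 and 8 and the synopsis row show otherwise.
- A reader might infer from the short list in SAP section 11, which names only reportable adverse events, that the DMEC will not see non-serious severe hypoglycaemia. That list says what the data will include and does not set a limit. Protocol 11.5 and 17.2 have the DMEC review compiled adverse event data with no seriousness limit, and 11.2.3 requires a form for every severe episode.
- A reader might infer from the contrast with criterion 7 that criterion 6 is a slip of the pen. That is plausible, but the documents do not state the intent.

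**Conclusion.** The point holds as a minor safety wording correction. No item in 9.15 names recurrent severe hypoglycaemia related to closed loop, and the one item that names hypoglycaemia excludes it. Action then depends on judgement, on voluntary exit, or on a discretionary synopsis reason missing from the section that sites would apply.

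The practical gap is small. That assessment assumes that investigators apply the 11.1.4 definition of seriousness as written and use criterion 8 when they should. The documents give no rate of device-related severe hypoglycaemia for this population, so no number of affected participants is offered. Sample size, power, alpha and the primary result are unaffected.

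**What to change.** Make three edits in 9.15:

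1. Reword criterion 6 to: *Recurrent severe hypoglycaemia, whether or not judged related to closed loop use.*
2. Add item 12, matching the synopsis and kept discretionary: *Serious adverse events, where the investigator so decides after weighing benefit against risk.* Criterion 7 can stay as it is, because item 12 also gives serious DKA a named reason in either arm and from any cause.
3. Extend the cross-reference for the mixed meal test and HbA1c invitation from items 5 to 11 to items 5 to 12.

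The cost is one phrase, one line and one number in a protocol amendment. No new data are needed: 11.2.3 already requires an adverse event form for each severe episode, and SAP section 8 already reports relatedness to the device. The downside is that a few closed-loop participants may stop the device, which would slightly lower closed-loop use in the intention-to-treat comparison. They would remain in follow-up under the existing provisions.
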